## Abstract

Invasive meningococcal disease (IMD) causes significant morbidity and mortality worldwide with serogroup B being the predominant serogroup in Australia and other countries for the past few decades. The licensed 4CMenB vaccine is effective in preventing meningococcal B disease. Emerging evidence suggests that although 4CMenB impact on carriage is limited, it may be effective against gonorrhoea due to genetic similarities between *Neisseria meningitidis and Neisseria gonorrhoeae*. This study protocol describes an observational study that will assess the effect of the 4CMenB vaccine against meningococcal carriage, IMD and gonorrhoea among adolescents in the Northern Territory (NT). All 14–19-year-olds residing in the NT with no contraindication for 4CMenB vaccine will be eligible to participate in this cohort study. Following consent, two doses of 4CMenB vaccine will be administered two months apart. An oropharyngeal swab will be collected at baseline and 12 months to detect pharyngeal carriage of *Neisseria meningitidis* by PCR. The main methodological approaches to assess the effect of 4CMenB involve a nested case control analysis and screening method to assess vaccine effectiveness and an Interrupted Time Series regression analysis to assess vaccine impact. Research ethics approvals have been obtained from Menzies and Central Australian Human Research Ethics Committees and the Western Australian Aboriginal Health Ethics Committee. Results will be provided in culturally appropriate formats for NT remote and regional communities and published in international peer reviewed journals. ClinicalTrials.gov Identifier: NCT04398849.

## 1. Introduction

Invasive meningococcal disease (IMD) caused by *Neisseria meningitidis* is a rare but serious infection and an important cause of mortality worldwide [1,2]. Clinically it presents as meningitis and or septicaemia, with a case fatality rate between 4.1–20.0% [3]. *N. meningitidis* is classified into serogroups based on the biochemical composition of the capsular polysaccharide, with serogroup B causing the majority of IMD in Europe, Australia, New Zealand and much of America [4].

Exposure to *N. meningitidis* is common in the general population, resulting in asymptomatic oropharyngeal carriage that may be transient, or long-term [5]. Age influences carriage, with an increase from 15 years to a peak at around 19 years [6]. The United Kingdom introduced the meningococcal B vaccine (4CMenB^®^, Bexsero^®^) into its national immunization program for infants and toddlers in 2015 and the vaccine was shown to protect children under the age of 2 years from IMD [7]. However, 4CMenB does not have significant effects on carriage of disease-causing meningococci, including group B [8].

Emerging evidence suggests that 4CMenB may protect against gonorrhoea, a sexually transmissible infection (STI) which is identified by the World health Organisation as a public health priority. An estimated 106 million cases of gonorrhoea are diagnosed worldwide each year with the number increasing in recent years [9]. Gonococcal infections commonly present as urethritis in males and cervicitis in females, but mucosal infections of rectum, pharynx and eye frequently occur [10,11,12]. In addition, gonococcal infections can lead to pelvic inflammatory disease, adverse pregnancy outcomes, infertility and neonatal complications. In Australia, gonorrhoea notifications increased by 80% over a 5-year period from 2013 to 2017 (from 65.5 to 118 per 100,000) [13]. The Northern Territory (NT) has the highest rate of gonorrhoea notifications in Australia with 686.6 per 100,000 reported in 2017 [14]. The gonorrhoea notification rate in the Aboriginal and Torres Strait Islander population was 6.6 times higher than the non-Indigenous population in 2017 (627.5 per 100,000 versus 95.6 per 100,000) [13]. A recent study on potential disseminated gonococcal infection between January 2010 and September 2018 reported 106 cases in the Top End of the NT. Of these, 94 (88.7%) were among Indigenous Australians and the highest incidence was in the 15–19 year old age group [15]. Variations exist across regions within the NT, which is divided into two major areas; the Top End which covers 516,945 square kilometres and a population of approximately 250,000 and Central Australia, which covers 830,220 square kilometres and a population of approximately 41,000. The Central Australian region communities have much higher notification rates than the Top End communities.

The effectiveness of antibiotics for gonorrhoea has been compromised due to emerging resistance to broad-spectrum Cephalosporins, and development of an effective gonorrhoea vaccine has been challenging. However, surveillance reports from Cuba, New Zealand and Canada showed a decline in gonorrhoea incidence following vaccination against *N. meningitidis* [10,11,12,16]. A recent transmission-dynamic model showed that a vaccine conferring 31% protection (as estimated for the MeNZB) for 2–4 years could reduce the incidence of gonorrhoea by 45% by 2030 [17].

In addition to having the highest rates of gonorrhoea, the NT also has the highest rate of IMD in Australia with 2.0 per 100,000 reported in the first 6 months of 2019 [18]. Carriage prevalence of *N. meningitidis* is higher in Aboriginal people than in non-Aboriginal people [8]. As the NT has the highest burden of both gonorrhoea and meningococcal disease in Australia, this is an important setting to conduct the proposed study.

The aim of this study is to implement a 4CMenB vaccination program for young people aged 14–19 years of age, residing in the NT and to evaluate the effectiveness of the vaccine on gonorrhoea, meningococcal carriage and IMD.

## 2. Materials and Methods

Exclusion criteria include anaphylaxis following any component of the Bexsero^®^ vaccine, previous receipt of the MenB vaccine, Bexsero^®^ (previous receipt of MenNZB^TM^ is allowed), known pregnancy, clinical conditions representing a contraindication to intramuscular vaccination and venepuncture. A temporary exclusion of a 14-day interval between receipt of study vaccine and COVID-19 vaccines applies. Eligible 14–19-year-olds can participate in the study via schools or via government and non-government immunisation clinics including Aboriginal Community Controlled Health Organisations (ACCHO). The 14–19-year-old age group is selected to enable vaccination prior to rapid carriage and STI acquisition. Conducting the study in schools provides an opportunity to use the existing school immunization program and infrastructure in a closed accessible environment with potential for the highest rates of participation. The objectives and outcome measures are detailed in Table 1.

### 2.1. Study Population

All 14–19-year-olds residing in the NT are eligible to participate. It is expected that a large number of the participants will be Aboriginal and Torres Strait Islander young people comprising 40% of the population of the NT, the highest proportion of Indigenous people in any Australian state or territory Australian Bureau of Statistics. Estimates of Aboriginal and Torres Strait Islander Australians [19]. Of the 14–19-year-old Aboriginal and Torres Strait Islander Australians residing in the NT, approximately, 52% live in outer regional areas, 19% live in remote and 29% live in very remote regions Australian Bureau of Statistics. Estimates of Aboriginal and Torres Strait Islander Australians [19].

### 2.2. Study Processes

Immunisation providers will receive training in all study procedures, including informed consent, collection of posterior oropharyngeal swabs and 4CMenB vaccination.

Those participating via the school program will require written/electronic informed consent from the parent/guardian. Those participating via health clinics will be able to provide written consent for themselves if they are aged 16 years and above and parental/guardian consent will be required for those under 16 years. Participants and parents are provided with the contact details of the study coordinators to obtain any additional information that they may require prior to or after receiving the vaccination.

Participation includes three visits (Figure 1). During visit one, the participants will be asked to complete a one-page de-identified questionnaire to obtain information on characteristics that are known to be relevant to carriage of *N. meningitidis* including smoking/tobacco history, household size, recent respiratory tract infections and recent use of antibiotics. The immunisation providers will then obtain an oropharyngeal swab which will be placed immediately in STGG transport medium (skim milk, tryptone, glucose and glycerine; Thermo-Fisher Scientific Australia) [20] and transported to NT Pathology [21]. The immunisation provider will then administer the first dose of the licensed 4CMenB vaccine. The second visit will be scheduled a minimum of 2 months after the first visit and an SMS reminder will be sent 2 days prior to the scheduled date to notify parents/guardians/participants of the follow up visit. During the second visit, the participants will receive the second dose of the 4CMenB vaccine. The required minimal time interval between the 4CMenB vaccine and other vaccines including the COVID-19 vaccine will be maintained based on prevailing guidelines. The third visit will be scheduled 12 months after the first visit and a similar SMS reminder will be sent. During the third visit, the participants will be asked to complete the same study questionnaire that was completed at visit one and the second posterior oropharyngeal swab will be obtained. All participants will receive a $20 value voucher at visits 1 and 3 to reimburse them for their time.

All collected data including consent forms, questionnaires and swab analysis results will be securely stored on a password-protected database held by the Adelaide Health Technology Assessment, The University of Adelaide. Range and logic checks will be performed on all collected data.

### 2.3. Patient and Public Involvement

The study materials will be reviewed by a Youth Advisory Group and an Aboriginal Advisory Group at several stages. Public, Independent, Catholic, Christian and Lutheran schools in the NT will provide information to parents/guardians and students and support the roll out of the study in schools. The ACCHOs will provide information about the study to their communities and support the roll out in clinics. A multimedia communication strategy has been developed by a public relations/communications company in collaboration with the media team of the University of Adelaide. Key strategies include website development (B Part of it NT. Available online: bpartofitnt.com.au (accessed on 17 January 2022)), brand identity ‘B Part of it NT’, a Facebook page, advertising and creating supporting material in English and up to 10 Aboriginal languages to be used in remote settings, a flip chart explaining the study in a simplified version to be used alongside the participant information sheets, ambassador engagement, public relations and management and media training. Participants and parents are encouraged to provide feedback on the study using the B Part of it NT Facebook page.

### 2.4. Ethics and Dissemination

The study has been approved by the Human Research Ethics Committee (HREC) of the Northern Territory Department of Health and Menzies School of Health Research (Reference Number: 2019-3507), the Central Australian HREC (Reference Number: 2019-3524) and the Western Australian Aboriginal Health Ethics Committee (Reference Number: 996). The progress of the study will be communicated to all stakeholders via monthly newsletters. The final study results will be provided to participants, parents/guardians, stakeholders and the general public via media including television, radio and print media. Results will be provided in culturally appropriate ways as advised by the Aboriginal advisory Group and Youth advisory group including use of media. The results will be presented at local, national and international scientific meetings and published in peer reviewed journals.

### 2.5. Study Safety Monitoring and Surveillance

Vaccine safety and adverse events will be routinely monitored through an enhanced passive surveillance system used for timely detection of adverse events following immunisation through the NT Department of Health, Centre for Disease Control (CDC). Participants/parents are given the contact details of the Immunisation Unit of the NT Centre for Disease Control and advised to report any AEFI to the Immunisation Unit. Serious adverse events (SAEs) which are considered to be related to administration of 4CMenB will be reported to the HRECs, the study sponsor, the Therapeutic Goods Administration (Australian Government) and the vaccine manufacturer within 72 h of the site becoming aware of the SAE. A study vaccine safety committee comprising independent vaccine safety experts has been established and will review all study-related vaccine safety data in accordance with a vaccine safety surveillance protocol. Monthly summaries of all reported adverse events will be provided to the vaccine safety committee and the vaccine manufacturer.

### 2.6. Training of Immunisation Providers

Immunisation nurses will be trained in obtaining posterior oropharyngeal swabs to ensure a standardised collection technique. Training manuals and a training video including standard swab collection will be available at all sites for continuous training. Schools and clinics will be randomly selected for monitoring of protocol-related study processes including consent and technique of obtaining the throat swab.

### 2.7. Laboratory Processes

On receipt of samples at NT Pathology, DNA will be extracted using automated extraction on the Roche MagnaPure system and subjected to PCR screening for the presence of specific meningococcal DNA (using PorA gene detection). Any sample yielding a positive PCR will be identified and cultured for *Neisseria* species on selective and non-selective agar and incubated overnight in CO_2_ at 35 °C. Plates will be examined daily for isolates up to 72 h. *N. meningitides* will be identified by standard diagnostic laboratory bacteriological methods using oxidase reaction and MALDI with further PCR testing to determine the capsular group (A, B, C, W, X, Y). Genomic DNA will be extracted and sequenced via the Illumina platform. Raw reads will undergo quality control and trimming to ensure only high-quality reads are analysed. Relevant typing data, resistance markers, and phylogenetic analyses will be carried out using several software tools [22].

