### 4.2. N. meningitidis Carriage

Carriage prevalence of all and each disease-causing genogroups of *N. meningitidis* (A, B, C, D, E, X, W, Y) and non-groupable *N. meningitidis* among 14–19-year-olds detected by PCR at 12 months will be compared with the results obtained at baseline using logistic regression. The difference in carriage at 12 months compared to baseline will be expressed as an odds ratio (OR) with 95% CI. Adjustments will be made for gender, age, smoking, ethnicity, remoteness area, household size (number of persons/room) as available and appropriate.

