7. Estimate the difference in carriage prevalence of each disease-causing genogroup of *N. meningitidis* (A, B, C, E, X, W, Y) in 14–19-year-olds at baseline compared to 12 months after receiving two doses of 4CmenB.	Detection of each disease-causing genogroup of *N. meningitidis* (A, B, C, E, X, W, Y) by PCR at baseline and at 12 months.
8. Estimate the difference in carriage prevalence of non-groupable *N. meningitidis* in 14–19-year-olds at baseline compared to 12 months after receiving two doses of 4CMenB.	Detection of all non-groupable *N. meningitidis* by PCR at baseline and at 12 months.
9. Describe the acquisition of all and invasive *N. meningitidis* after receiving two doses of 4CMenB.	Acquisition of *N. meningitidis* (negative at baseline, positive at 12-month follow-up) as measured by PCR.
Meningococcal disease	
10. Estimate the vaccine impact and effectiveness of 4CMenB administered to young adults on group B IMD in 14- to 19-year-olds	Notifications of group B IMD in the 4CMenB vaccinated population compared to the unvaccinated population.
	Notifications of IMD in the six years preceding 4CMenB vaccination compared to three years post vaccination (Interrupted time series analysis).
11. Estimate the vaccine impact and effectiveness of 4CMenB administered to young adults on group B IMD in all ages	4CMenB vaccination status in the population with IMD, compared to the general population (Screening method).
	4CMenB vaccination status in the population with IMD, compared to randomly selected controls from the Australian Immunisation Register (Case–control method).
Risk factors	
12. Identify characteristics associated with gonorrhoea in 15–19-year-olds.	Risk factors associated with gonorrhoea in 14–19-year-olds.
13. Identify characteristics associated with carriage of all genogroups of *N. meningitidis* in 14–19-year-olds at baseline and 12 months.	Risk factors associated with carriage of all genogroups of *N. meningitidis* in 14–19-year-olds at baseline and 12 months.
14. Identify characteristics associated with carriage of disease-causing genogroups of *N. meningitidis* (A, B, C, E, W, X, Y) in 14–19-year-olds at baseline and 12 months.	Risk factors associated with carriage of disease-causing genogroups of *N. meningitidis* (A, B, C, E, W, X, Y) in 14–19-year-olds at baseline and 12 months.
Cost effectiveness	

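### Section 2.7, read naturally, ties capsular grouping to cultured isolates, leaving porA-positive swabs without an isolate no stated route to a genogroup for objectives 6-8

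*Protocol article*

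**What the plan says.** **Laboratory sequence (protocol article, section 2.7).** DNA is extracted from the swab and "subjected to PCR screening for the presence of specific meningococcal DNA (using PorA gene detection". Next, "Any sample yielding a positive PCR will be identified and cultured for" *Neisseria* species. "Plates will be examined daily for isolates up to 72 h". *N. meningitidis* then "will be identified by standard diagnostic laboratory bacteriological methods using oxidase reaction and MALDI with further PCR testing to determine the capsular group", the groups listed being A, B, C, W, X and Y. Genomic DNA extraction and sequencing come last.

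**Outcomes.** In Table 1, objective 7 is measured as "Detection of each disease-causing genogroup of" *N. meningitidis*, and objective 8 as "Detection of all non-groupable" *N. meningitidis*. Objective 6 covers all disease-causing genogroups together. All three are stated as PCR detection at baseline and at 12 months, and none mentions culture. Section 4.2 says that these categories, "detected by PCR at 12 months will be compared with the results obtained at baseline using logistic regression".

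**Primary carriage outcome.** Objective 2 is carriage of any *N. meningitidis* by PCR. It can be scored from the porA result alone.

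**The concern.** The laboratory text and the outcome definitions do not clearly describe the same measurement. If the group PCR is run on isolates, the genogroup endpoints are in effect PCR-positive and culturable, whereas the outcome table says PCR-positive. A swab that is porA-positive but grows nothing is a carrier for objective 2 and has no group for objectives 6-8. It could be coded negative for every group, non-groupable or missing. The three codings give different results, and the article does not choose between them.

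Non-groupable carriage is the most exposed, because it is naturally a residual class. A swab tested with no capsular target found differs from a swab never group-tested, and the two should not be merged. Objective 9 (acquisition of invasive meningococci) and objective 14 (risk factors for disease-causing genogroups) also need a group for each positive swab.

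The carriage comparison is before-after, with no concurrent unvaccinated arm in the model. If culture yield did change between visits, nothing in the design would cancel it.

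**Working it through.** **1. The passages side by side.** Oxidase and MALDI identify what has grown on the plates. In section 2.7 the group PCR sits in that same sentence, after the plates have been read for isolates. It is not attached to the porA screen described earlier. Hence the natural reading is grouping of isolates. The sentence does not name the material tested, however, and does not say that culture-negative swabs go ungrouped. Where Table 1 means isolates it says so (objectives 16 and 17); objectives 6-8 do not.

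**2. The plan's own carriage figure.** Inputs from section 2.9.2: baseline prevalence p1 = 0.068; 20% reduction, so p2 = 0.0544; correlation 0.25; two-sided alpha 0.05; 30% loss. For paired proportions:
- p11 = p1·p2 + 0.25·√(p1q1p2q2) = 0.0037 + 0.0143 = 0.0180
- discordant proportion pd = (0.068 − 0.0180) + (0.0544 − 0.0180) = 0.0865 from unrounded values; d = 0.0136
- n = (1.96·√pd + 0.8416·√(pd − d²))² / d² = 3,667; 3,667 / 0.70 = 5,239, as stated
- at 90% power, 4,908 / 0.70 = 7,011 to 7,012, against 7,011 stated

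These figures concern overall carriage and do not change.

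**3. Expected positive swabs at N = 5,239.**
- Baseline: 5,239 × 0.068 = 356
- 12 months, 70% returning: 3,667 × 0.0544 = 200 with the planned reduction, or 3,667 × 0.068 = 249 with no change

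**4. Swabs without a group, if grouping needs an isolate.** Yield y is not in the document, so the values are assumptions. Number ungrouped = positives × (1 − y), using 200 positives at 12 months.

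| Assumed y | Baseline | 12 months | Total |
|---|---|---|---|
| 90% | 36 | 20 | 56 |
| 70% | 107 | 60 | 167 |
| 50% | 178 | 100 | 278 |

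If ungrouped swabs are coded negative, each genogroup's observed prevalence is y times its true value. With rare outcomes the standard error of the log odds ratio grows by about 1/√y: 1.05, 1.20 and 1.41 at these yields.

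**5. Non-groupable class.** Let s be the true non-groupable share of positives. If ungrouped swabs are placed in that class, the observed share is s·y + (1 − y). This exceeds s by (1 − y)(1 − s), which is never negative.

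**6. Effect on the odds ratio.** Observed prevalence is y0·p at baseline and y1·p at 12 months when carriage does not truly change. Using p = 0.068 for illustration:
- 80% at both visits: OR 1.00
- 80% then 70%: OR = (0.0476/0.9524) / (0.0544/0.9456) = 0.87
- 70% then 80%: OR 1.15

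With a true 20% reduction and equal 50% yields, OR = (0.0272/0.9728) / (0.034/0.966) = 0.79. The full-data value, (0.0544/0.9456) / (0.068/0.932), is also 0.79. Equal yields cost precision and level, and leave the ratio essentially unbiased.

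**7. A related mismatch.** Section 2.7 lists A, B, C, W, X, Y. Table 1 adds E, and section 4.2 adds D and E. The boundary of non-groupable is therefore unclear for a second reason.

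**The case against.** The strongest reply is that section 2.7 is ambiguous rather than contradictory. The further PCR may refer back to the porA PCR and use the swab extract, which already exists at that point. That reading agrees with Table 1 and section 4.2. Even grouping of isolates is done by PCR, as the outcomes say. The article also condenses a full protocol, which the Data Availability statement says exists, and section 2.10 points to a separate analysis plan. The coding of undetermined swabs could properly sit in either.

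Much of this stands. The document does not establish that grouping happens only after culture, or that culture-negative swabs cannot be scored. The absence of a coding rule alone would not be a finding. What remains is that the article prints a specific sequence which, followed as written, most naturally leaves some carriers ungrouped, although a better route is available from material already in hand.

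A reader might also infer that the plan would produce a false vaccine effect on disease-causing groups, even one matching the 20% reduction in section 2.9.2. The documents do not support that. It requires a particular fall in yield between visits for which they give no evidence, and the 20% target belongs to overall carriage, which rests on porA PCR. Section 2.2 describes posterior oropharyngeal swabs at visits 1 and 3 and the same questionnaire, covering recent antibiotics, at both.

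**Conclusion.** The point holds as a mismatch between the natural reading of the laboratory sequence and the outcome definitions for secondary objectives 6-8. On that reading, genogroup prevalence is understated by the share of porA-positive swabs that yield no isolate, precision falls accordingly, and non-groupable carriage is overstated if ungrouped swabs are put there. Across assumed yields of 90% to 50%, some 56 to 278 of about 556 positive swabs would be affected at N = 5,239. These counts rest on assumed yields and on the plan's prevalence, return and reduction figures. The direction of each effect does not depend on the exact yield.

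The 12-month versus baseline odds ratio for a genogroup is biased only if yield differs between visits, and nothing in the document shows that it would. Primary objective 2 and the stated sample sizes are unaffected. If group PCR is already run on the swab extract, the defect is one of wording.

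**What to change.** - State in section 2.7 that capsular-group PCR is run on the DNA already extracted from every porA-positive swab, regardless of culture result.
- Base objectives 6-8 on that result, and likewise the group-specific parts of objectives 9 and 14.
- Report swabs that could not be group-tested as genogroup undetermined, separate from non-groupable, with counts at each visit.
- Keep culture for sequencing.
- While editing, align the list of groups across section 2.7, section 4.2 and Table 1.

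A DNA-load threshold for calling a swab non-groupable is not needed for this correction, and the document offers no basis for setting one.

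**Cost.** Capsular PCR on existing extracts: about 556 swabs at N = 5,239 with the planned reduction (356 + 200), or about 744 at N = 7,011 (477 + 267). Only those with no isolate are additional to grouping by isolate. No new swabs, visits or consent steps are needed, and the sample size does not change.
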